### Access to data

The principal investigator will have access to the final study data and make the final decision to terminate this study. No other research staff will have access to any data acquired in this study.

### Monitoring

Monitoring will be performed by one of our research staff according to the standard operating procedures and the results will be given to the principal investigator within 2 weeks after monitoring. When adverse events or other unintended effects of the intervention happen, the principal investigator will perform appropriate treatments for the participant, report the incident to the Nagasaki University Hospital Clinical Research Ethics Committee (REC) and share this information with the research staff. A data monitoring committee is not necessary because DH treatment with Nanoseal or CAREDYNE Shield is general practice and a low-invasive intervention procedure.

### Potential benefits and harms

This study will contribute to future clinical improvements. However, atopic dermatitis is a potential side effect of the intervention.

## Discussion

Several limitations associated with the present study warrant mention. First, blinding of operators will not be performed; therefore, the risk of bias in this domain may be unavoidable. Second, the data will be collected just after the participant’s training. Thus, VRS which is easier to understand for participants than a visual analog scale (VAS) will be performed; however, VRS is considered to be less sensitive than VAS [18, 19]. Third, it has been recommended that at least three different stimuli, specifically tactile, cold and air stimuli, should be used for clinical assessments of DH because DH may differ among stimuli [2]. However, only air stimuli will be evaluated in the present study because this study is being performed for sample size calculations, which is based on the primary outcome: the reduction of pain intensity in response to air stimuli. Tactile stimuli will be evaluated as a secondary outcome in a future, large-scale study. The GI and PI will be used as secondary outcomes in the present study. If a reduction in either is observed, the effectiveness of CAREDYNE Shield for the reduction of the GI and PI will be investigated in a future clinical study.

Desensitizers like CAREDYNE Shield and Nanoseal that induce chemical occlusion of dentinal tubules are biocompatible and react only with tooth substance; they can, therefore, be casually applied to subgingival areas and proximal surfaces. Furthermore, for several decades, in-vitro studies have investigated the function of zinc and reported that zinc reduced the demineralization of enamel and dentin and inhibited dentin collagen degradation, plaque growth and biofilm formation [20–24]. Thus, CAREDYNE Shield, which releases zinc ions, may be a useful novel desensitizer that acts not only as a desensitizer but also as a root caries inhibitor.

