### Randomized allocation

After enrollment, baseline assessments will be performed by the examiner who enrolled the participant in this study. Randomized allocation will then be performed in a 1:1 ratio by the dentist in charge of the patient with opaque, sealed envelopes prepared before participant recruitment and on which “Nanoseal” or “CAREDYNE Shield” is printed. Participants allocated to the intervention group will be treated with CAREDYNE Shield, while those allocated to the control group will be treated with Nanoseal. The information on the desensitizers used in this study is described in Table 4.

**Table 4 Tab4:** Desensitizers used in this study

**Material**	**Manufacturer**	**Composition**
CAREDYNE Shield	GC Dental Industrial Corporation, Tokyo, Japan	Solution A: fluorozinccalciumsilicate glass Solution B: 10–15% phosphoric acid
Nanoseal	Nippon Shika Yakuhin Co., Ltd., Shimonoseki, Japan	Solution A: fluoroaluminocalciumsilicate glass Solution B: 10% phosphoric acid

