### Intervention

After randomized allocation, the participants in the intervention group will be treated with CAREDYNE Shield, and those in the control group will be treated with Nanoseal by the operator who performed allocation. Prior to the application of CAREDYNE Shield or Nanoseal, dental prophylaxis and water rinse will be performed to remove plaque deposits; the areas to be treated will be isolated with cotton rolls and dried with cotton pellets; two equal proportions of solution A and solution B will be mixed with a micro-brush and applied to the dentin surface for 20 s, followed by rinsing with water. Four weeks after the treatment, clinical assessments will be performed by the examiner who enrolled the participant in this study.

During this study, any other dental treatment to DH teeth are prohibited, and all intervention procedures will be recorded by the operator in an electronic chart to improve adherence to intervention protocols. Discontinuing intervention will be performed in the following case: (1) participant requests to stop or change the allocated intervention, (2) worsening disease or new disease occurs or (3) continuing this study is judged to be inappropriate.

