### Secondary outcome

Secondary outcomes are the change in the gingival condition near the treated area measured with the Gingival Index (GI) and the change in the oral hygiene status at the treated dentin surface measured with the Plaque Index (PI) from baseline to 4 weeks after the intervention [16, 17]. The GI and PI will be evaluated with inspection and palpation.

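### The trigger for taking GI and PI forward names no comparator or size, and baseline precedes a plaque-removing prophylaxis in both arms, so it is likely to be met with no CAREDYNE Shield effect

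*Protocol article*

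**What the plan says.** Five statements in the protocol article bear on this point.

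- **Secondary outcome.** Both indices are defined as changes over time within the participant. For plaque the outcome is "the change in the oral hygiene status at the treated dentin surface measured with the Plaque Index (PI) from baseline to 4 weeks" after treatment, and GI is defined over the same period.
- **Randomized allocation.** "After enrollment, baseline assessments will be performed by the examiner who enrolled the participant in this study". The next step is: "Randomized allocation will then be performed in a 1:1 ratio by the dentist in charge of the patient". Baseline scoring therefore comes before allocation, and treatment follows allocation.
- **Intervention.** "Prior to the application of CAREDYNE Shield or Nanoseal, dental prophylaxis and water rinse will be performed to remove plaque deposits". This applies to both arms and falls between the baseline and 4-week scores.
- **Statistical design.** Only the primary outcome is given a test (Fisher's exact), and the section closes by ruling out any further analysis.
- **Discussion.** The use to be made of the secondary outcomes is: "If a reduction in either is observed, the effectiveness of CAREDYNE Shield for the reduction of the GI and PI will be investigated" in a later clinical study.

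**The concern.** The prophylaxis acts directly on plaque, which is what PI scores, and it is given after baseline to every participant. Any part of its effect that lasts to 4 weeks appears as a fall from baseline in both arms, whichever product was applied. The Discussion's condition asks only that a reduction be seen in one of the two indices. It does not ask whether the reduction is larger than under Nanoseal, or larger than chance.

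The Nanoseal arm receives the same cleaning and would remove its effect in expectation. Neither the condition nor the planned analysis uses that arm for GI or PI.

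At stake is the usefulness of the two secondary outcomes. This is a pilot meant to inform later work, and the Discussion sentence is the only stated use of GI and PI. If the condition is likely to be met whatever the product does, meeting it says little about CAREDYNE Shield, and a further study could be started on that basis.

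**Working it through.** **Is there a figure to reproduce?** The protocol gives no error rate for this trigger. The only related figure is the sample size, which supplies the number of completers. Fifteen per group with 20% dropout gives 15 / 0.8 = 18.75, so 19 per arm and 38 in total, consistent with the stated 40. With 20 per arm and 20% dropout, 20 × 0.8 = 16 complete.

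**Inputs**

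| Input | Value | Source |
|---|---|---|
| Completers per arm, n | 16 (15 and 20 also tried) | Sample size section, as above |
| Product effect on GI and PI | 0 | The null case under examination |
| Fall in mean index not due to the product, s, in SDs of the change score | 0 to 0.5 | Assumed; the document gives none |
| GI-PI correlation of changes, ρ | 0 to 0.8 | Assumed; the document gives none |

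**Formula.** Take the condition as a negative mean change in GI or PI in the CAREDYNE Shield arm. Each mean change divided by its standard error is approximately normal with mean −s√n and variance 1. The condition fails only if neither mean falls:

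P(met) = 1 − Φ₂(−s√n, −s√n; ρ),

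where Φ₂ is the bivariate normal distribution function. At s = 0 this reduces to 1 − [1/4 + arcsin(ρ)/(2π)].

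**No lasting prophylaxis effect (s = 0), any n**

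- ρ = 0: 1 − 0.25 = 0.75
- ρ = 0.5: 1 − (0.25 + 0.0833) = 0.67
- ρ = 0.8: 1 − (0.25 + 0.1476) = 0.60

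These values owe nothing to the prophylaxis. They arise because any fall counts, however small, and because either index suffices.

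**Same fall in both indices, n = 16 (√n = 4).** For example, with s = 0.2 and ρ = 0, each index fails to fall with probability Φ(−0.8) = 0.212, so P(met) = 1 − 0.212² = 0.955.

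| s | ρ = 0.8 | ρ = 0.5 | ρ = 0 |
|---|---|---|---|
| 0.05 | 0.68 | 0.74 | 0.82 |
| 0.1 | 0.75 | 0.81 | 0.88 |
| 0.2 | 0.86 | 0.91 | 0.96 |
| 0.3 | 0.93 | 0.96 | 0.99 |
| 0.5 | 0.99 | >0.99 | >0.99 |

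If only one index falls, by 0.3 SD, the range is 0.89 to 0.94. Results with n = 15 or 20 are similar.

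**Using the control arm.** In a between-arm difference the shared prophylaxis effect cancels in expectation (s = 0). If each index were tested at an assumed one-sided 0.025, at least one would trigger in 1 − 0.975² = 4.9% of null trials at ρ = 0, and in 3.9% at ρ = 0.8. If any between-arm difference in the favourable direction were enough, the figure would again be 60-75%. The comparator removes the prophylaxis effect; a criterion is still needed to deal with chance.

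**The case against.** **The sentence makes no efficacy claim.** It only says that a question will be studied later. This stands. A reader might infer that the pilot would report a gingival or plaque benefit of CAREDYNE Shield, but no section plans such a report. The cost is a weakly founded further study.

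**The reference point is not stated.** The aim and design are comparative, so a reduction relative to Nanoseal could be meant. This stands in part: the fall from baseline is inferred from how the Secondary outcome section defines the indices. But no section states a between-arm GI or PI comparison, and the Statistical design section leaves no room for one. Even on the comparative reading, a rule without a size is met by chance in 60-75% of null trials.

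**The condition is not certain to be met.** This stands. A reader might infer that cleaning guarantees it. The document does not say how much of the prophylaxis effect remains at 4 weeks, and a small lasting fall leaves the probability well short of 1 (68-82% at 0.05 SD).

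**The 60-75% figures do not measure confounding by prophylaxis.** Correct. They measure the missing threshold and the choice of either index. The prophylaxis accounts for the rise above them.

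**This is one Discussion sentence, and details may sit in a fuller document.** The sentence does not touch the primary outcome, its analysis or the sample size. But the point concerns a rule that the article states, together with its explicit exclusion of further analyses, and not a detail left out.

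**Conclusion.** The concern holds in a limited form. As written, the condition cannot separate a CAREDYNE Shield signal from cleaning given to everyone, and it is likely to be met with no product effect. The chance is about 60-75% with no lasting prophylaxis effect, 86-96% with a shared fall of 0.2 SD and at least 99% with 0.5 SD.

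These figures rest on reading a reduction as a fall in the arm mean from baseline, on 16 completers, on assumed falls and correlations, and on a normal approximation. GI and PI are ordinal, and exact ties at no change would lower the probabilities slightly. The direction of the conclusion does not depend on the exact values, since the condition is met more often than not across the whole assumed range.

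The consequence is confined to the decision on a future GI/PI study. The point should be corrected, but it does not threaten the trial's main result.

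**What to change.** 1. **Discussion.** Replace the condition with one based on the randomised comparison, for example: GI and PI at 4 weeks will be compared between arms (CAREDYNE Shield minus Nanoseal), adjusted for baseline, with 95% confidence intervals; they will be taken forward only if the estimate meets a criterion stated in advance; changes within each arm are descriptive and are not attributed to the desensitizer. The investigators choose the criterion, since the document offers no basis for a particular value.
2. **Statistical design.** Amend the closing exclusion of further analyses so that it permits this comparison. Otherwise the two sections would conflict.

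The cost is two wording changes and a small amount of extra analysis on data already being collected, with no added visits or participants. The downside is that the condition will be met less often, and with about 16 completers per arm the intervals will be wide.

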## Data Availability

Not applicable

## Abbreviations

CONSORT: Consolidated Standards of Reporting Trials
DH: Dentin hypersensitivity
RCT: Randomized clinical trial
REC: Research Ethics Committee
SPIRIT: Standard Protocol Items: Recommendations for Interventional Trials
UMIN-CTR: The University Hospital Medical Information Network-Clinical Trials Registry
